### Planned inclusion and exclusion criteria

Suitable patients older than 18 years, suffering from CLR of at least 4 months or more and with concordant findings on either MRI or CT are included. Included patients must also have a VAS score of at least 6/10 (at presentation) and must be ready to provide informed patient consent for participating in the study as a blind subject.

Exclusion criteria would include any patient having an absolute contraindication to neuraxial injection in the form coagulation disturbance anticoagulant therapy, bleeding disorder, or infection at the site of injection; patients with anatomical deformity or derangement, either congenital or acquired such as extreme scoliosis, previous implant or instrumentation, making it difficult to access the foramen as evidenced by MRI, CT, or plain X-rays; patients with cancer to account for their symptoms; patients with known significant psychiatric history; patients unable to communicate effectively in English; patients with allergy to local anesthetics or radiographic dye; patients with a history of acute neurological weakness or neurodeficit in the affected limb in terms of measurable motor weakness or abnormal reflexes.

### Duration of treatment and follow-up

Duration of treatment period will involve approximately 30 to 60 min of actual intervention done in the OR. The duration of complete follow-up will be for 3 months after the intervention with the following interval follow-up assessments: (1) 30 min post-procedure in recovery, (2) 24 h after - by a phone call (only VAS and side effects); (3) at 1 week post-procedure visit to the assessor (VAS, ODI, medications, side effects); (4) at 4 weeks post-procedure visit to the observer for assessment for success (VAS, ODI, medications, side effects); (5) at 2 months post-procedure-visit to observer (VAS, ODI, medications, side effects); (6) at 3 months post-procedure visit to the observer - last follow-up visit (VAS, ODI, medications, side effects).

### Primary and secondary outcome measures

#### Primary

1. Recruitment rate: percentage of suitable patients fulfilling the inclusion–exclusion criteria, recruited for the actual study after informed consent. The final assessment will be after the complete recruitment, at which time all the expected number of subjects (*n* = 32) must have been enrolled. Criteria for success would be as expected recruitment of at least four patients per month after fulfilling the selection criteria and with full informed consent with at least 80% of eligible patients fulfilling the selection criteria being recruited.

2. Percentage of patients continuing to be participants for the whole study.

Participants retain the right to withdraw from the study at any point. However all participants after intervention shall be included in the final analysis, on intention to treat principle. Any participant requesting for a withdrawal shall be given the option of continuing medical care or epidural or transforaminal ESI at the next available opportunity (present standard of care).

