## Methods/design

### Methodology and techniques

Patients would be screened at St Joseph Hospital, Hamilton, Canada, at their-East End Pain Clinic for CLR of at least 4 months’ duration. Based on the history and clinical examination, a diagnosis of CLR involving one or more spinal segments is made and noted. The patient is considered eligible for the study if a CT or MRI of lumbar spine done within the last 4 months demonstrates pathology that is concordant with the patient’s clinical symptoms. The spinal level(s) targeted for treatment will be based on clinical findings, for example if a patient exhibits signs and symptoms of right L4 radiculopathy, and the MRI demonstrates right paracentral disc herniations at both L4-5 and L5-S1, only the L4 DRG will be targeted. Patients fulfilling the inclusion criteria will be fully explained about the nature of study, interventions involved and the possible complications after which an informed consent will be taken. Enrolled patients would be randomized according to the method described and included in the study according to previously randomized order. He/she will also meet the assessor (blind to intervention), who would note down the baseline parameters of the patient and also collect a baseline ODI score along with noting down other parameters. A patient having bilateral radiculopathy will be treated for his most affected side in the trial. A patient having CLR of more than one segment on one side shall be treated for all the involved segments with the same technique and counted as a single procedure or intervention for the study. After checking for the informed consent and other safety checklist, patient will only be revealed as belonging to the study (not mentioning whether it is a placebo/actual treatment). All operating room (OR) personnel, including the physician performing the intervention and the patient, shall be blind to the randomization and treatment. The grouping code, hence the actual treatment will only be known by the person operating the RF machine. Only the RF technician shall be in view of the working details of the RF machine and the noise of the machine is cut by playing out a music or song. This ensures blinding of all involved, except the RF technician. All interventions will be done as day-care procedures in the OR. Patients would continue to use their medications as before. If the pain relief obtained necessitates decrease in the usage of medications that shall be recorded. Similarly unsatisfactory pain relief obtained necessitating increase in the dose or change of medications shall be recorded. The other parameters to be used for statistical analysis are collected as mentioned under data analysis. The patient will have an established IV access. He would be put in prone position. The involved area of back would be made sterile using chlorohexidine 2% and draped. The patient would be connected to continuous monitoring of 3 lead ECG, NIBP, and pulse oximetry. Sedation, if used will be minimal (Grade I or II) to obtain the necessary response of the patient. Under fluoroscopy guidance particular spinal segment(s) affected is (are) identified and confirmed. LA using 2% lidocaine is infiltrated to the skin at entry site. For both groups a RF needle (Bayliss: 22-G needle, 5-mm curved active tip and 10 cm) is used. With an appropriate fluoroscopy view the needle is inserted to the target location in both the groups.

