### Trial design, outline, and flow chart

#### Sample size, recruitment rate

Sample size has been determined based on feasibility considerations. Total duration of recruitment planned is 8 (clinically active) months. The proposed target is recruitment for 8 months, with an expectation of at least four patients every month, with a total of 32 patients for the study. Potential to recruit patients, as four patients every month has been calculated based on the transforaminal steroid injections (TFESI) performed in the last 3 to 6 months and booked for the next 3 to 6 months (calculated as monthly) at St Joseph’s Healthcare; data obtained from St Joseph’s Healthcare, Department of Anesthesia and Pain. TFESI represents a well-accepted, presently performed intervention for patients of CLR and most patients suitable for that are potential recruits for this study.

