## Discussion

The results of this pilot study would primarily give us information about the patient recruitment and study methodology. This is being done as there are no previous studies (RCTs) to indicate the successful effects of PRF in CLR. The initial study proposal was to conduct an RCT comparing PRF-DRG with TFESI, which have proven to be more successful than midline ESIs for lumbar radiculopathy [52], and are probably the most effective intervention available. However our literature search showed that so far, there were no RCTs involving sufficient participant numbers to evaluate the efficacy of PRF. The only RCT by Van Zundert *et al.*[16] on cervical radicular pain had only 19 participants in either group. Keeping this in mind we devised this proof of concept study to evaluate the efficacy of PRF as compared to placebo.

It is very challenging to devise and conduct a placebo controlled trial in interventional pain medicine. Because of the nature of the problem, which involves significant suffering for a long time, patients may be unwilling to participate as blind participants. CLR patients would have had a trial of most medications and simple interventions before they go on to have complex spinal interventions, such as PRF-DRG. It may also be difficult to have such patients to be under long periods of follow-up after a blind intervention, especially if it is not of benefit to the patient. This trial would be able to tell us whether we were able to recruit patients as expected for the trial and also whether they continue to be participants of the study for the whole duration. The other important and novel aspect of this study which merits attention is the technique of patient blinding during the procedure. Although we will not be formally evaluating the blinding process, it will be interesting to know if we faced significant challenges and if such a methodology needs to be appropriately modified for a future trial. The study would also assess the outcomes of pain relief from PRF compared to placebo. Apart from telling us if PRF is successful, the study would also indicate the difference in pain relief in terms of absolute reduction in VAS scores. This is necessary to assess the number of study participants for a future trial. The assessment of side effects is included to understand if there are major or minor side effects and risks which need to be better studied and informed to the patients.

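### The denominator of the 80% recruitment criterion is not securely defined: read literally, patients who refuse consent drop out of it

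*Protocol article*

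**What the plan says.** All references are to the protocol article.

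- **Primary and secondary outcome measures, Primary, item 1** defines the recruitment rate as the "percentage of suitable patients fulfilling the inclusion–exclusion criteria, recruited for the actual study after informed consent". Success has joint conditions: "recruitment of at least four patients per month after fulfilling the selection criteria and with full informed consent", all 32 expected subjects enrolled, and "at least 80% of eligible patients fulfilling the selection criteria being recruited". Item 2 makes retention a second primary outcome.
- **Planned inclusion and exclusion criteria** lists, beside age, duration of pain, concordant imaging and the VAS threshold, that patients "must be ready to provide informed patient consent for participating in the study as a blind subject".
- **Methodology and techniques** gives a sequence: diagnosis and imaging, then an explanation of the study to patients who meet the inclusion criteria, then consent.
- **Sample size, recruitment rate** sets the target: "Total duration of recruitment planned is 8 (clinically active) months", "with an expectation of at least four patients every month, with a total of 32 patients for the study".
- **Discussion** gives a reason why uptake is in doubt: "patients may be unwilling to participate as blind participants".

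**The concern.** A recruitment percentage is informative only if people who could have joined and refused are counted below the line. Here the denominator is the set of patients who meet the inclusion and exclusion criteria, and willingness to consent as a blind subject is one of those criteria. Applied as worded, a refusal turns a suitable patient into an ineligible one. The percentage can then fall only through losses that occur after a patient has already agreed.

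At stake is the one component of the recruitment outcome expressed as uptake among suitable patients. A sham-controlled procedure in patients with long-standing pain may well be refused, and the pilot is meant to inform a larger trial. If refusals are invisible in the 80% figure, the planners of the larger trial could take high acceptability from a number that does not measure it. They could then underestimate how many patients must be screened.

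**Working it through.** **Inputs.** From the protocol: 4 patients per month, 8 months, 32 patients in total, threshold 80%. The protocol gives no consent rate, so rates from 30% to 90% are assumptions used to show the range.

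**1. The plan's own figure.** 4 per month × 8 months = 32. This reproduces the stated total.

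**2. The rule read literally (decliners outside the denominator).** With 32 enrolled and no loss after agreement, the rate is 32/32 = 100%, whatever share of suitable patients refused. Only later losses can lower it. Take 40 willing patients and an assumed later loss of 5% or 10%. The binomial probability that at least 32 of the 40 (80%) are enrolled is then 0.9999 or 0.98.

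**3. The rule with decliners counted.** The largest eligible pool compatible with the threshold is 32/0.80 = 40, so at most 40 − 32 = 8 decliners. For an assumed consent rate c:

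- clinically eligible patients needed for 32 enrolled = 32/c
- clinically eligible patients needed per month for four recruits = 4/c
- chance of passing with 40 approached = P(at least 32 of 40 consent), binomial with probability c

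| Assumed c | Eligible (32/c) | Per month (4/c) | Rate, decliners in | Rate, literal | P(at least 32 of 40) |
|---|---|---|---|---|---|
| 50% | 64 | 8.0 | 50% | 100% | 0.0001 |
| 60% | 53 | 6.7 | 60% | 100% | 0.006 |
| 70% | 46 | 5.7 | 70% | 100% | 0.11 |
| 80% | 40 | 5.0 | 80% | 100% | 0.59 |
| 90% | 36 | 4.4 | 90% | 100% | 0.98 |

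In the 50% row, 32/64 has a Wilson 95% interval of 38.1% to 61.9%, wholly below 80%. The same screening log would be reported as 100% under the literal rule.

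**4. Do the other conditions make up for this?** Only in part. The monthly count does fall with refusals: at c = 30% the clinic would need 4/0.30 = 13.3 clinically eligible patients a month. But a busy clinic can offset refusals. With 8 eligible patients a month and half refusing, four a month and 32 in 8 months are both reached. Retention is measured after enrolment and carries no information on refusal.

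**The case against.** The strongest reply is that the literal reading is not what was meant. Methodology and techniques has patients fulfil the inclusion criteria first, hear about the study next, and consent last, so a decliner has already been counted. The outcome definition also names the selection criteria and informed consent separately. If consent were already inside the denominator, that wording would be redundant and an 80% threshold would have little purpose. The Discussion says the trial should show whether patients could be recruited as expected. This stands: a non-circular reading exists and is probably the intended one. It does not settle the matter, because it conflicts with the list of inclusion criteria and no section states that decliners count as eligible.

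Three stronger inferences are tempting and are not supported:

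- **That the whole primary outcome is met almost automatically.** Success also needs four patients a month and 32 enrolled, retention is a separate primary outcome, and refusals still lower the monthly count. Only the 80% component is affected.
- **That Methodology and techniques contains a second, imaging-only definition of eligibility.** The sentence "The patient is considered eligible for the study if a CT or MRI of lumbar spine done within the last 4 months demonstrates pathology" could be taken that way in isolation. It goes on to require concordance with symptoms. The text before it requires at least 4 months of pain and a clinical diagnosis, and the text after it refers to patients who fulfil the inclusion criteria. It describes a screening step.
- **That refusals will go unrecorded.** Statistical tests plans a flow diagram, and feasibility outcomes as counts and proportions. It does not say whether refusals will be itemised, so this neither proves nor repairs the problem.

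**Conclusion.** The concern holds for the 80% component of the recruitment outcome. Its denominator is badly fixed: the inclusion criteria and the outcome definition together remove decliners, the order of procedures implies that they remain, and nothing decides between the two. The size of the discrepancy depends on the unknown refusal rate. At an assumed 50% consent it is 100% against 50%, a pass against a clear failure. At 90% consent both readings pass. No refusal figure appears in the protocol, so this shows what the rule can do and not what has happened in the trial. The definition should still be corrected, because it governs a primary success threshold and the other criteria do not measure uptake among suitable patients.

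**What to change.** For this outcome, define:

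- **Denominator:** all screened patients who meet the clinical and imaging inclusion criteria (age, at least 4 months of pain, concordant CT or MRI, VAS threshold) and have no exclusion, counted before the consent request and including those who decline.
- **Numerator:** patients randomised.
- **Reporting:** the number of refusals, with reasons where recorded.

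Willingness to consent remains a condition for entering the trial but is not used to define eligibility for this percentage. The abstract, the procedures, the criteria list and the outcome definition should all use the word eligible in this one sense.

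The cost is one reworded definition and a re-tabulation of the screening log, with no change to treatment or sample size. Trial status reports two participants still to be recruited, and the final assessment is set for after complete recruitment, so at that point the definition could still be fixed beforehand. Two limits apply. The re-tabulation is possible only if the log recorded patients who declined; if it did not, that should be reported. The resulting percentage may also be less favourable than one calculated without decliners.

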**Methods/designs:**

This is a single-center, parallel, placebo-controlled, triple-blinded (patients, care-givers, and outcome assessors), randomized control trial. Participants will have a history of chronic lumbar radicular pain for at least 4 months in duration. Once randomized, all patients will have an intervention involving fluoroscopy guided needle placement to appropriate dorsal root ganglion. After test stimulation in both groups; the study group will have a pulse radio frequency treatment at 42°C for 120 s to the dorsal root ganglion, with the control group having only low intensity test stimulation for the same duration. Primary outcome is to recruit at least four patients every month with 80% of eligible patients being recruited. Secondary outcomes would be to assess success of intervention through change in the visual analogue scale measured at 4 weeks post intervention and side effects. Allocation to each group will be a 1:1 ratio with allocation block sizes of 2, 4, and 6.

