### Primary research question

Is it feasible to do a larger scale clinical study to study the effectiveness of ‘PRF treatment of DRG as compared to placebo’ in CLR? Feasibility (outcome) parameters studied: (1) recruitment rate; (2) percentage of patients who go on to complete the full study after enrolling as participants.

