## Trial status

We are presently recruiting study participants. The trial is registered on clinicaltrials.gov with the unique identifier NCT01117870. We only require two more participants to complete the recruitment process. We have also completed interventions on 28/32 patients.

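### The analysis set called intention to treat is defined by having had the procedure, although patients are randomised before it

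*Protocol article*

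**What the plan says.** The analysis population is described once, under the primary outcome measures. After noting that "Participants retain the right to withdraw from the study at any point", the article continues: "However all participants after intervention shall be included in the final analysis, on intention to treat principle".

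The timing of randomisation comes from two other places. Methodology and techniques states, after informed consent, that "Enrolled patients would be randomized according to the method described and included in the study according to previously randomized order". It then describes the baseline assessment and, later, the procedure: "All interventions will be done as day-care procedures in the OR". The abstract gives the same order: "Once randomized, all patients will have an intervention involving fluoroscopy guided needle placement to appropriate dorsal root ganglion".

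Retention, the second primary feasibility outcome, is defined in the primary research question as the "percentage of patients who go on to complete the full study after enrolling as participants". The matching item under the primary outcome measures gives no denominator. The Statistical tests section promises a flow diagram and feasibility outcomes as counts and proportions, but defines no analysis set.

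**The concern.** Intention to treat means that everyone randomised is analysed in the allocated group. A set that depends on having had the procedure begins later than randomisation. Someone who withdraws while waiting for the operating-room visit is then randomised but outside the set as worded.

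Two things are at stake. The first is the comparison of 4-week pain response, which the Discussion intends to use when sizing a larger trial. With about 16 patients per arm, each exclusion removes 1/16 = 6.25% of an arm. The second is clarity about retention. The sentence on the final analysis stands directly under the retention item, so a reader could carry the treated-only denominator over to an outcome that the primary research question counts from enrolment. Losses before a blinded sham procedure are among the losses that a feasibility study should show.

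**Working it through.** **1. The plan's own figure.** The sample size section plans 8 months of recruitment "with an expectation of at least four patients every month, with a total of 32 patients for the study". 8 × 4 = 32, which reproduces. Allocation is 1:1, so 16 per arm if exactly balanced. No power calculation is involved; the question is which patients are counted.

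**2. Order of events.** Methodology and techniques runs: consent, randomisation of enrolled patients, baseline with the blinded assessor, operating-room procedure. The abstract agrees. Withdrawal is allowed throughout, so it can fall between randomisation and procedure. The stated set starts at the procedure. Randomised and analysed sets coincide only if nobody is lost in between.

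**3. What the Trial status section shows.** Two more participants are needed, so 32 − 2 = 30 have been recruited. It also reports "We have also completed interventions on 28/32 patients". Recruited but not yet treated: 30 − 28 = 2, or 2/30 = 6.7%. The other two of the 32 had not been recruited. Both untreated patients may simply have been waiting for their procedure.

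**4. Retention.** Let u be the number randomised but never treated. The document does not give u, so 0 to 4 is an assumed range. If every treated patient completes, retention from enrolment is (32 − u)/32:

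| u | Treated | Enrolment denominator | Treated denominator |
|---|---|---|---|
| 0 | 32 | 100% | 100% |
| 1 | 31 | 96.9% | 100% |
| 2 | 30 | 93.8% | 100% |
| 3 | 29 | 90.6% | 100% |
| 4 | 28 | 87.5% | 100% |

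For 28/32 the Wilson 95% interval is 72% to 95%.

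**5. Response at 4 weeks, with assumed counts.** Take 8/16 responders on pulsed radiofrequency and 4/16 on placebo, and count untreated patients as non-responders for this illustration only. The difference among all randomised patients is 50.0 − 25.0 = 25.0 points. Treated-only differences are:

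- All untreated in the active arm: u = 1, 8/15 − 4/16 = 28.3 points; u = 2, 8/14 − 4/16 = 32.1; u = 3, 8/13 − 4/16 = 36.5.
- One untreated in each arm: 8/15 − 4/15 = 26.7 points.
- One untreated, in the placebo arm: 8/16 − 4/15 = 23.3 points.

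The shift can go either way, and is small when losses are balanced.

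**The case against.** The strongest reply is that exclusion is inferred. The sentence does not restrict the analysis to treated patients in so many words. It follows the right to withdraw, so its main purpose is evidently to keep treated patients who later leave. That stands, and it is why the omission of untreated patients is described here as implied. It does not make the label right: no other sentence brings those patients in, and the one rule given is tied to the procedure.

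The article also does not say when the sealed envelopes are opened. If that happened in the operating room, the gap would nearly close. The text as written nevertheless places randomisation before the procedure in both the abstract and the methods.

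Several stronger readings are tempting, and the document does not support them:

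- *The status figures prove dropout.* They are a snapshot of a trial still recruiting, and they show a lag between recruitment and treatment.
- *The protocol computes retention among treated patients only.* The primary research question counts it from enrolment, so 28/28 = 100% is not the document's rule. The treated-denominator column above shows only what a misapplied denominator would give.
- *Patients whose needle position cannot be confirmed are dropped.* The article does not say so, and such a patient has arguably had the intervention that the abstract describes.
- *The randomised comparison is broken.* Patient, physician and assessor are blinded, and only the operator of the radiofrequency machine knows the allocation. Withdrawal before the procedure should therefore depend little on arm, and the main cost would be precision. The 28- to 36-point figures need every loss to fall in one arm.

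Finally, detailed population definitions are often left to a fuller plan. That excuses silence, but here the article states a population and misnames it.

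**Conclusion.** The point holds in a limited form. The set as worded is a treated, or modified intention-to-treat, population called intention to treat, and a randomised but untreated patient is omitted by implication. This conclusion rests on randomisation taking place at enrolment, as the article describes.

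No actual loss is documented. The size depends on u, which is unknown. For an assumed 1 to 4 untreated of 32, with all others completing, the two retention denominators differ by 3.1 to 12.5 percentage points. The effect on the response comparison is probably small given the blinding, and efficacy is a secondary outcome of a feasibility trial. The severity is moderate: it should be corrected before analysis, but it does not threaten the trial.

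**What to change.** Replace the sentence with a statement that all randomised participants are analysed in the group to which they were randomised, whether treated or not. In addition:

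- report randomised but untreated patients by arm in the flow diagram already planned;
- state under the primary outcome measures that retention is counted from enrolment or randomisation, in line with the primary research question;
- label any treated-only analysis as modified intention to treat or as a sensitivity analysis.

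The cost is a few sentences and possibly a few more patients in the denominators. Retention and success proportions may be slightly lower than on a treated-only count, for example the 96.9% to 87.5% retention shown above. Follow-up visits are timed from the procedure, so an untreated patient may have no 4-week outcome. How to handle that missing value is a separate choice among acceptable methods and need not be settled by this change.
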